#### GMT-errorless learning condition

The experimental treatment consists of GMT with an errorless learning approach, i.e., both the acquisition and application of GMT will be taught using error controlling methods. This implies active guidance from a therapist to prevent the occurrence of errors or guessing. Therefore, errorless learning techniques, such as verbal instructions, modeling and cue cards will be used, as well as written instructions of the chosen (i)ADL tasks. After the two tasks have been subdivided into multiple steps and have been rehearsed verbally during sessions 3 and 4, the actual execution of these steps is practiced in sessions 5 and 6 of the treatment. In these sessions cues will be faded after successful execution of the steps (i.e., without hesitation or errors). In sessions 7 and 8 the patient will be taught to check after each task step if the action was performed correctly and if it has led to the planned (subordinate) goals. ‘Checking’ is part of the final stage of the GMT algorithm and therefore both treatment goals will be fully integrated into the GMT algorithm and errorless execution of both complex tasks according to the GMT algorithm will be practiced.

#### GMT-trial and error learning condition

In the conventional GMT errors are allowed to occur. Patients will learn to use the GMT algorithm and the performance of the tasks using trial and error learning. In this condition the therapist is not required to prevent errors during the application of the GMT strategy, but he/she only provides feedback in response to errors (i.e. afterwards). Also, therapists will not provide clues as how to solve problems and will not actively prompt or guide the execution of tasks. After having chosen two (i)ADL tasks in sessions 1 and 2, session 3 consists of a general description of the GMT algorithm by the therapist. In sessions 4 and 5 the participant is asked to define the task steps and- complete the GMT schemes for both treatment goals. The therapist will not help in defining the task steps and the main aim is to motivate the participant to complete the schemes. If errors occur, the therapist will not intervene, and the participant will have to detect these during the training. In sessions 6 and 7 the actual performance of the (i)ADL tasks will be practised, again using the above described trial and error approach. The participant will be motivated to actively practice performance and to seek solutions in the case of problems. Session 8 is again devoted to the execution of the tasks and to eventually improve the execution of task steps or the previous completed GMT schemes.

### Objectives

The primary objective of this investigation is to examine the efficacy of a combined errorless learning and GMT intervention for the treatment of executive problems in patients with acquired brain injury (ABI). These patients are in the chronic phase of their illness and the study will focus on individually chosen complex daily tasks ((i)ADL), such as cleaning a bathroom, processing mail or preparing a meal. The hypothesis is that brain-injured patients will (re)learn performance of (i)ADL tasks more efficiently if an errorless learning method is used. That is, more task steps will be performed correctly and in the right sequence and less irrelevant and missing steps will be present. Consequently, more goals and sub goals will be attained by applying errorless learning in GMT.

### Outcomes

An overview of the outcome measures is given in Table 
2. The main outcome will be (i)ADL task performance. Performance of each task step will be scored on a 3-point scale: 0) *absence/incomplete*: the task step is missing or incomplete; 1) *questionable/ineffective*: the task step is not correctly performed or not set in the correct sequence; 2) *competent/correct*: the task step is successfully performed and set in the correct sequence. Observed total scores will be converted into percentage scores to allow statistical comparison of data from different (i)ADL tasks, and comparison between groups. A similar scale was used in previous research
[27] to assess (i)ADL task performance in patients with Alzheimer’s dementia. Task execution will be filmed and evaluation by using the scale will take place afterwards by an assessor who is not involved in the actual treatment to secure the blind nature of the design.

**Table 2 T2:** Recruitment- and outcome variables

**Outcome measure**	**Measurement**	**Recruitment**	**Baseline**	**Post-treatment**
**Primary outcome measure**				
*(i)ADL task performance*	Standardized scale evaluating task steps		X	X
***Secondary outcome measure***				
*Goal attainment*	Goal attainment scale		X	X
**Neuropsychological assessment**				
*Executive functioning*	Brixton spatial anticipation test	X		X
	Category fluency test	X		X
	Go/No-go task, subtest TAP	X		X
	Letter fluency test	X		X
	Letter number sequencing, subtest WAIS III	X		X
	Modified six elements test	X		X
	Zoo map test, subtest BADS	X		X
*Memory*	Rivermead behavioural memory test-third edition	X		X
*Attention & Concentration*	Alertness task, subtest TAP	X		X
*Estimation IQ*	National adult reading test (Dutch version)	X		X
**Questionnaires**				
*Subjective cognitive functioning*	CFQ (Cognitive failures questionnaire)		X	X
*Dysexecutive behaviour*	DEX (Dysexecutive questionnaire)		X	X
*Self-reported executive functioning*	EFI-NL (Executive function index)		X	X
*Observed executive functioning*	EOS (Executive observation scale)		X	X
*Quality of life*	RAND 36-item short form health survey		X	X

A secondary outcome measure will be goal attainment using Goal Attainment Scaling (GAS)
[46]. GAS is an individualized method to evaluate the extent to which individual treatment goals are achieved by defining several levels of outcomes (‘as expected’, (much) more than expected, (much) less than expected). GAS is scored in a standardized way to allow statistical comparisons between individual treatment goals and is widely used in rehabilitation
[47,48]. During session 2, GAS schemes for both treatment goals will be completed by the trainer in cooperation with the participant. During the post-treatment measurement, two GAS scores will be obtained, one by the patient and one by the trainer.

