**Methods/Design:**

The study is a double blind randomized controlled trial, in which the efficacy of Goal Management Training with an errorless learning approach will be compared with conventional Goal Management Training, based on trial and error learning. In both conditions 32 patients with acquired brain injury of mixed etiology will be examined. Main outcome measure will be the performance on two individually chosen everyday-tasks before and after treatment, using a standardized observation scale and goal attainment scaling.

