### Interventions

Both treatment arms will comprise eight one-hour individual sessions, administered twice a week by trained therapists. An overview of the content of the training sessions is shown in Table 
1. Sessions 1–4 will take place at the participating centers. Sessions 5–8 will take place at the participants’ home or in the work environment, depending on the treatment goals. The first two sessions of GMT will be identical for both conditions. In the first session participants will be informed about GMT in general and about cognitive dysfunction, more specifically about executive dysfunction after acquired brain injury. In the second session each participant will choose two individual treatment goals. These treatment goals must be (i)ADL tasks and the participant has to experience difficulties performing the chosen tasks. Learning the correct execution of these (i)ADL tasks will be the main aim during the rest of the training sessions. Acceptable treatment goals are those which can be subdivided into multiple steps and should be defined in accordance with the SMART method (Specific, Measurable, Attainable, Reasonable, Timely)
[45]. After the second session a baseline assessment will take place. The execution of both treatment goals will be filmed, so that it can be evaluated later by assessors who are blind for allocation. After the baseline assessment participants will undergo training sessions 3–8 in the errorless learning condition or in the trial and error condition.

**Table 1 T1:** Content of GMT sessions for both treatment arms

**Session**	**Contents**	
1	Providing information about training;	
	Providing information about cognitive functioning after acquired brain injury in general with an emphasis on executive impairments;	
	Increasing awareness of individual executive dysfunction;	
	Preparing the setting of two individual treatment goals	
2	Setting two individual chosen treatment goals (i)ADL tasks);	
	Filling out the Goal Attainment Scale forms for each treatment goal	
	**GMT-errorless learning**	**Conventional GMT-treatment**
3	Defining steps concerning treatment goal 1 using cue cards and other errorless learning techniques	General information about GMT and the GMT algorithm
4	Defining steps concerning treatment goal 2 using cue cards and other errorless learning techniques	Filling out GMT scheme by participant concerning treatment goal 1

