### Post-treatment

After treatment, (i)ADL task performance will be assessed again by filming and scoring task performance. The previous completed GAS schemes will be scored by participant and by trainer to evaluate goal attainment. The questionnaires and neuropsychological assessment, using parallel versions of the same tests, will be administered after treatment as well, to control for nonspecific recovery. The data gathered with the questionnaires and the neuropsychological tests provide measures for change in insight, executive complaints, subjective and objective executive functioning for moderator analyses, to examine possible determinants for treatment success.

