### Statistical analysis

All data will be analyzed with IBM SPSS 19. The normality of all variables will be checked and corrected for, if necessary. The performance on the neuropsychological tests will be compared with normative data and corrected for age and education. Descriptive statistics of relevant variables will be obtained and compared for the two treatment arms using analysis of variance.

To evaluate the efficacy of GMT-errorless learning compared to conventional GMT with trial and error learning, pre- and post training data will be analyzed using a 2 × 2 repeated measure analysis of variance (General Linear Model) with treatment condition (GMT-errorless learning and conventional GMT) as between-subject factor and measurement (pre- and post-treatment) as within-subject factor. The dependent variable will be the standardized scale score (quantitative). The same analysis will be done for the secondary outcome measure, the GAS scores. Appropriate post-hoc tests will be performed and effect sizes (partial eta-squared) will be computed. Moreover, correlations will be computed between moderator variables (questionnaires and neuropsychological tests) and treatment effects (difference score: post treatment minus baseline).

The background variables of the participants in both treatment conditions are expected to be comparable (age, education level, estimation IQ) because of the randomization procedure. In case of significant differences, appropriate statistical adjustment for confounding variables will be performed (ANCOVA). All statistical tests will be two-tailed, alpha set at 0.05.

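### One of the two goal attainment scores tested between arms comes from the trainer, who very probably knows the allocation; the trial's blinding covers the filmed task scale and the participant, not this score

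*Protocol article*

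**What the plan says.** **Who scores GAS.** The Outcomes section (paragraph after Table 2) states that "two GAS scores will be obtained, one by the patient and one by the trainer". The Post-treatment section repeats it: "The previous completed GAS schemes will be scored by participant and by trainer to evaluate goal attainment". The scales are set up earlier: "During session 2, GAS schemes for both treatment goals will be completed by the trainer in cooperation with the participant".

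**Who delivers treatment.** The Interventions section describes "eight one-hour individual sessions, administered twice a week by trained therapists". Sessions 3 to 8 differ by arm. In the errorless condition the therapist guides actively so that errors do not happen. In the conventional condition the therapist gives feedback only after errors.

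**What is blinded.** The abstract says "The study is a double blind randomized controlled trial", and the opening of Methods/Design uses the same label. Randomization and blinding describes two measures. Participants are not told how the arms differ. Task performance is filmed and scored by research assistants who take no part in the training. No blinded rating of GAS is described.

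**Rank and analysis.** The abstract's main outcome is performance on the two chosen tasks, "using a standardized observation scale and goal attainment scaling". The body ranks GAS lower: "A secondary outcome measure will be goal attainment using Goal Attainment Scaling (GAS"), and Table 2 agrees. Under Statistical analysis, "The same analysis will be done for the secondary outcome measure, the GAS scores"; this refers to the 2 × 2 repeated measures analysis of variance (arm by pre/post).

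**The concern.** A therapist who has taught a patient by one method is asked to judge how far that patient's goals were met, and that judgement enters a comparison of the two methods. If the therapist expects the new method to do better, the score can lean that way without any difference in what patients can do. The authors took care to keep treatment staff away from scoring the task scale, but the same care is not described for GAS.

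Two features of the text make this matter more. The double-blind label carries no limit, so a reader of the results could take the trainer's GAS score as blind. And the abstract places GAS within the main outcome, so a favourable trainer-rated result could be presented with more weight than the body of the article gives it.

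**Working it through.** **Step 1: does the trainer know the arm?** The article uses both trainer and therapist and never says that they are the same person. Two places point that way. The Background section on errorless learning lists modelling by the trainer among the teaching techniques, and the trainer completes the GAS schemes with the participant in treatment session 2. Whoever delivers sessions 3 to 8 must know the arm, because the two conditions prescribe opposite conduct when an error is about to occur. If trainer and therapist are one person, the trainer's post-treatment score is unblinded.

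**Step 2: which outcome ratings are blinded?**

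| Rating | Rater | Blinding described |
|---|---|---|
| Task scale (primary in the body) | Research assistants, from film | Yes |
| GAS, patient's score | Participant | Intended: arm differences withheld |
| GAS, trainer's score | Trainer | None |

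Only the third row is open.

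**Step 3: how much could a tilt matter?** The documents give no estimate of rating bias, so the tilts below are assumptions.

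Inputs: 32 per arm (Sample size); two-tailed alpha 0.05 (Statistical analysis); no true difference between arms; trainer's ratings shifted by *b* SD in favour of one arm. With two arms and two time points, the arm-by-time test is equivalent to a two-sample *t* test on the change, so *b* is in SD units of the score compared.

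- Degrees of freedom: 32 + 32 − 2 = 62; critical value about 2.00.
- Noncentrality: *b* × √(32/2) = 4*b*.
- False-positive rate: P(|T| > 2.00), with T noncentral *t* on 62 df.

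| Assumed tilt *b* | Noncentrality | Two-sided false-positive rate |
|---|---|---|
| 0 | 0 | 5.0% |
| 0.1 SD | 0.4 | 6.8% |
| 0.2 SD | 0.8 | 12.4% |
| 0.3 SD | 1.2 | 21.9% |

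These rates apply to a test of the trainer's score only.

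**Step 4: rank of GAS.** The abstract gives two instruments for the main outcome. Table 2, Outcomes and Statistical analysis give one primary measure (the task scale) and call GAS secondary. The body agrees with itself; the abstract does not match it.

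**Step 5: baseline GAS.** Table 2 marks GAS at both baseline and post-treatment, and the pre/post analysis needs both. The Outcomes and Baseline sections describe only completing the schemes at session 2; Outcomes and Post-treatment describe scoring only after treatment. The table and the text need to be reconciled.

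**The case against.** The best reply is that the design is blind where it matters most. The primary outcome is scored from film by independent assistants. One of the two GAS scores comes from a participant kept uninformed about the difference between arms. The blinding section says what the label covers, and nowhere claims that the trainer is blind. The GAS schemes are written jointly with the participant in a session that is the same in both arms. All of this stands, and it limits the point to one rating of a secondary outcome.

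Several stronger readings are tempting but not supported:

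- **That GAS as a whole is unblinded.** It is not; the patient's score is meant to be blind.
- **That the trial has two primary outcomes, with a family-wise error of 1 − 0.95² = 9.75%.** The body has one primary outcome. The figure also assumes independent tests, which is implausible for two ratings of the same goals; positive correlation would lower it.
- **That no baseline GAS exists, so the pre/post analysis must be dropped.** Table 2 lists a baseline GAS. What is missing is agreement with the text, and an article may leave the scoring procedure to the full protocol.
- **That failing to name which GAS score is the endpoint is an error in itself.** That can properly be left to an analysis plan not shown here.

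What the reply does not remove is that the article states that the trainer scores GAS and that the GAS scores are tested between arms. A fuller document could restrict the test to the patient's score, but the text as it stands does not.

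**Conclusion.** The point holds for the trainer's GAS score alone. Followed as written, the plan would test between arms a score from a rater who very probably knows the allocation, in a trial called double blind without qualification. The blind-rated primary outcome is unaffected.

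The size of the bias is unknown. False-positive rates of about 7%, 12% and 22% follow from assumed tilts of 0.1, 0.2 and 0.3 SD; they show sensitivity and are not estimates. The conclusion also assumes that trainer and therapist are the same person, which is the natural reading but is not stated. The mismatch between abstract and body over the rank of GAS, and between Table 2 and the text over baseline GAS, are matters of wording to be reconciled.

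**What to change.** 1. Name one blinded GAS rating as the tested secondary endpoint, the same for all participants. Either the research assistants who already score the films assign the GAS level for each goal from those films, or the patient's own score is used. Do not switch between the two from patient to patient, since that would mix rater types within one endpoint.
2. Keep the trainer's score, reported as descriptive and labelled unblinded.
3. State that blinding applies to participants and to the video assessors.
4. Correct the abstract so that the task scale is the single primary outcome and GAS is secondary, as in Table 2 and the Outcomes section.
5. Reconcile the baseline GAS entry in Table 2 with the text: say whether and by whom GAS is scored before training, or amend the table and the GAS analysis to match.

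**Cost.** Items 2 to 5 are wording only. Film-based GAS in item 1 takes some rater time, some GAS levels may not be visible on film, and the result will overlap with the task scale because both would be read from the same recordings. The patient's score needs no new data collection, but it is a self-report from patients whose self-monitoring the article describes as impaired.

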#### Additional study parameters

##### Questionnaires

Questionnaires will be administered to measure several aspects of executive functioning. The Dysexecutive Questionnaire (DEX)
[49], both the patient and the proxy version, will be used for the assessment of dysexecutive behaviour. Self-reported executive functioning will be measured using the Dutch version of the Executive Function Index (EFI-NL)
[50]. The Executive Observation Scale (EOS) (based on Pollens
[51]), completed by a proxy, will be used as an observation measure for executive function. The Cognitive Failures Questionnaire (CFQ)
[52] will assess self-reported subjective cognitive complaints in general. Quality of life will be determined using the RAND 36-item Short Form Health Survey (RAND-36)
[53].

### Baseline

After the second session, in which two individual treatment goals ((i)ADL tasks) are established and the GAS schemes are completed by the trainer in cooperation with the participant, the baseline measurement will take place. During this assessment execution of both treatment goals will be filmed to secure the blind nature of the design. The recorded performance will be assessed by an independent research assistant using the standardized scale to guarantee blinding of condition.

### Post-treatment

After treatment, (i)ADL task performance will be assessed again by filming and scoring task performance. The previous completed GAS schemes will be scored by participant and by trainer to evaluate goal attainment. The questionnaires and neuropsychological assessment, using parallel versions of the same tests, will be administered after treatment as well, to control for nonspecific recovery. The data gathered with the questionnaires and the neuropsychological tests provide measures for change in insight, executive complaints, subjective and objective executive functioning for moderator analyses, to examine possible determinants for treatment success.

### Sample size

Determination of the sample size for this study is based on data from a RCT examining the effects of a structured 6-week Goal Management Training
[17]. In each group 32 participants are required to detect an effect size of *d =* .6 with a power = .80 and α. = 05. These estimated sample sizes are comparable with other studies evaluating the efficacy of different types of GMT
[17,54].

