#### Setting

Patients will be recruited from the Rehabilitation Medical Centre Groot Klimmendaal in Arnhem, the Netherlands and the outpatient rehabilitation clinic for brain injured patients and the department of Neurorehabilitation of the Sint Maartenskliniek in Nijmegen, the Netherlands. In the course of 18 months 64 participants will be recruited.

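### The sample size of 32 per group does not follow from the stated d = 0.6, 80% power and two-tailed alpha of 0.05; those inputs give 45 per group, and 32 gives about 66% power

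*Protocol article*

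**What the plan says.** The Sample size section of the protocol article gives an effect size, a power, an alpha and a result: "In each group 32 participants are required to detect an effect size of *d =* .6 with a power = .80". The same sentence fixes alpha at 0.05. Sidedness is set in the Statistical analysis section: "All statistical tests will be two-tailed, alpha set at 0.05".

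The abstract confirms equal arms of 32, and the Setting section plans the matching total: "In the course of 18 months 64 participants will be recruited".

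The planned primary analysis compares the arms over two measurements: "pre- and post training data will be analyzed using a 2 × 2 repeated measure analysis of variance (General Linear Model"), with treatment condition between subjects and measurement within subjects. The article does not say whether the SD behind d is that of the raw score or of the change score, and it gives no correlation between the pre- and post-treatment scores.

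**The concern.** The sentence presents 32 per group as what d, power and alpha require. A reader can check that with those three figures and the stated sidedness, and the check fails by 13 per group, or about 14 points of power. That is far more than rounding or the choice between a normal and a t calculation can explain.

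What is at stake is how the trial's sensitivity is described. At 80% power, one trial in five misses a true effect of the planned size. At 66% it is about one in three. A non-significant result would be read against the stated 80%, so that figure should be one that can be derived.

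**Working it through.** **Inputs.** n = 32 per group, d = 0.6, power 0.80 and alpha 0.05 (Sample size); two-tailed tests and a 2 × 2 repeated-measures ANOVA (Statistical analysis); 1:1 allocation (abstract).

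**Step 1. Try to reproduce 32 from the stated inputs.** For two independent means, the normal approximation is n = 2(z₁₋α/₂ + z₁₋β)² / d².

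- Two-sided: 2 × (1.960 + 0.842)² / 0.36 = 43.6, so 44 per group.
- One-sided: 2 × (1.645 + 0.842)² / 0.36 = 34.3, so 35 per group.

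The exact calculation with the noncentral t gives 44.6, so 45 per group two-sided, and 35.04, so 36 per group one-sided. None of these is 32.

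**Step 2. Power at 32 per group.** The noncentrality parameter is d × √(n/2) = 0.6 × √16 = 2.40, on 62 degrees of freedom.

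| Test | Power (noncentral t) | Power (normal) |
|---|---|---|
| Two-sided 0.05 | 65.6% | 67.0% |
| One-sided 0.05 | 76.7% | 77.5% |

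Solving for the effect instead, 32 per group has 80% two-sided power at d = 0.71.

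**Step 3. The test that is actually planned.** With two measurements, the arm-by-time interaction is equivalent to a t-test on change scores. There are two ways to scale d.

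- If d = 0.6 is in units of the change-score SD, Step 2 applies unchanged: 65.6% power, 45 per group.
- If d = 0.6 is in units of the raw-score SD (taken as equal at both times) and ρ is the pre-post correlation, the change-score SD is √(2(1 − ρ)) raw SDs. The effective size is then 0.6 / √(2(1 − ρ)).

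The second scaling gives, two-sided at 32 per group:

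| ρ | Effective d | Power | n per group for 80% |
|---|---|---|---|
| 0 | 0.424 | 39% | 89 |
| 0.3 | 0.507 | 51% | 63 |
| 0.5 | 0.600 | 66% | 45 |
| 0.6 | 0.671 | 75% | 36 |
| 0.65 | 0.717 | 81% | 32 |
| 0.7 | 0.775 | 86% | 28 |

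The break-even correlation follows from setting the effective size to the 0.7115 of Step 2: 1 − (0.6 / 0.7115)² / 2 = 0.644.

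**The case against.** The strongest reply is that the two-group t-test is not the planned test. The article plans a repeated-measures interaction, and Step 3 shows that 32 per group does give 80% power for it when d is on the raw-score SD and the correlation is about 0.64 or higher. This stands, and it limits the point. A reader might infer that the trial certainly lacks 80% power, or that the design needs 45 per group whatever the analysis. The documents do not support that, because the power of the planned test depends on two quantities they do not give. But the reply does not rescue the sentence as written, which derives 32 from d, power and alpha alone. Nor can a high correlation be presumed: the tasks are individually chosen and are trained between the two measurements, and below 0.5 the power is lower than 66%.

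One other calculation also returns 32: the between-subject main effect, averaged over both measurements, at a correlation of 0.4 (80.6% power). It assumes a difference of 0.6 at baseline as well as after treatment, so it does not describe the effect being tested.

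Three further inferences are tempting and should not be drawn.

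- **That d = 0.6 is the effect found in the earlier GMT trial, and so the wrong contrast.** The article says only that the determination of sample size is "based on data from a RCT examining the effects of a structured 6-week Goal Management Training". It does not say which data were used, and that trial report is not at hand.
- **That the lack of a dropout allowance is an error.** Recruiting 64 equals 2 × 32, but a condensed article may leave attrition to the full protocol, and no loss rate is given from which to compute its effect.
- **That adjusting for the baseline score settles the matter.** ANCOVA on baseline would need a correlation of only about 0.54, but the article reserves ANCOVA for background variables that differ between arms. The baseline score is not a planned covariate, so that threshold belongs to a different test.

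**Conclusion.** The sample-size statement is wrong as written: its own inputs, with the stated two-tailed testing, lead to 45 per group and not 32. With 32 per group the power for d = 0.6 is 65.6%, and the effect detectable with 80% power is 0.71. One-sided testing, which the article rules out, would not close the gap (36 per group, 76.7%).

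The arithmetic is certain for a two-group comparison, and for the planned interaction if d is on the change-score SD or the correlation is 0.5. It does not show that the planned test has less than 80% power. With d on the raw-score SD and a correlation of about 0.64 or higher, 32 per group is sufficient, but the article states neither condition.

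**What to change.** Correct the Sample size paragraph in one of two ways, according to where 32 came from.

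1. Keep 64 participants and restate the claim, for example: 32 per group gives about 66% power for d = 0.6 (two-sided 5%), or 80% power for d = 0.71.
2. If 32 came from a repeated-measures calculation, say so. State which SD scales d and the assumed pre-post correlation (about 0.64 or higher, with d on the raw-score SD) that yields 80%, with the basis for that correlation.

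Either change is a sentence or two and needs no extra patients or change to the analysis. The first option costs a less favourable power figure. The second makes the claim rest on an assumption that readers can then judge.
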